#### Effectiveness

Study Aims 2 and 3 examine the clinical outcomes of the TeleQuitMH program. For Aim 2 (*Determine the effectiveness of telephone counseling in promoting long-term abstinence from smoking among mental health patients*) there will be no control group, as these data will only be collected on patients who enroll in TeleQuitMH. We will calculate the percentage of participants with 30-day point prevalence abstinence at two and six months. We will also examine which baseline characteristics (e.g. age, race/ethnicity, self-efficacy, nicotine addiction, mental health diagnosis, symptom severity) are associated with abstinence, and we will use multivariable logistic regression to determine those characteristics that are independently associated with abstinence. For Aim 3 (*Compare the effectiveness of telephone counseling delivered by VA staff with that delivered by state quitlines*) we will calculate the 30-day point prevalence abstinence rates at two and six months separately for the two treatment arms and compare these rates using logistic regression, adjusting for covariables.

We based our power calculation on an ability to detect a difference in six-month abstinence between our two randomized groups. We expect the six-month abstinence rate will be 15% in the quitline arm and 20% in the VA arm. With an anticipated 1200 participants in each treatment arm, we will have >80% power to detect this 5% difference in abstinence rates between the two arms at the 0.05 significance level.

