## Methods/design

### Overview

Figure 1 provides an overview of the clinical effectiveness portion of the trial’s design. We are implementing a telephone care coordination program (called the Telephone Quality Improvement Trial in Mental Health, or “TeleQuitMH”) at six VA facilities. Mental health providers refer their smoking patients to the program via electronic medical record (EMR) consult. The program calls referred patients to offer enrollment using the patient’s phone numbers listed in the EMR. Enrolled patients receive smoking cessation medications and multi-session, proactive telephone counseling. In a one-to-one fashion, we randomize patients to receive the proactive telephone counseling from a VA counselor or their state quitline. We survey patients by phone at baseline, two months, and six months to assess outcomes. We are using four organizational- or provider-level interventions to optimize program implementation: blended facilitation, provider training, informatics support, and provider feedback. We are conducting a three-phase formative evaluation to identify barriers to and facilitators for program implementation.

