*VA counseling*: For patients randomized to receive counseling from a VA counselor, they are assigned a VA counselor trained to work with smokers who have a mental health diagnosis. The counselor provides structured counseling using a protocol that we created specifically for this study. The protocol includes proactive counseling and relapse-sensitive scheduling. The content is based on motivational interviewing (MI) and problem solving therapy and addresses both behavioral and cognitive issues, including motivation, self-efficacy, difficult situations, comorbid mental health symptoms, coping strategies, medication usage, and relapse prevention. The counseling includes planning (pre-quit) and follow-up (post-quit) sessions.

*Planning sessions*: The planning sessions last approximately 30–60 minutes and help patients develop an individualized quit plan. Content areas include smoking and quitting history, motivation, environmental factors, planning, proper use of quitting aids, and setting a quit date. Patients receive one to six planning sessions.

*Follow-up sessions*: Patients receive follow-up calls at 0, 1, 3, 7, 14, 21, and 30 days after their quit date. The calls are intended to prevent relapse and to help those who relapse or slip resume quitting. Follow-up calls, which last 10–15 minutes, also use a manual for consistency and fidelity monitoring. Participants are able to call the program staff in between scheduled calls if desired.

*State quitline counseling*: For patients assigned to state quitline counseling, a research assistant initiates a “warm transfer” of the patient to their quitline via a three-way call to start the counseling process. After the initial three-way call, study personnel are not involved in any aspect of the quitline counseling. The quitlines follow their regular service protocols, which are described in Table 2.

6. ***Follow****-****up***—All patients enrolled in the study receive a call from a research assistant at two and six months. Patients who are abstinent from smoking are congratulated, but these assessment calls do not provide counseling. Patients who have relapsed at six months are asked if they want to go through the program again.

**Table 2 T2:** Overview of state quitline services

**State**	**Typical number of counseling sessions**	**QL-initiated calls**	**Client-initiated calls**	**Typical length of first session (min)**	**Typical length of Follow-up sessions (min)**	**Free medications**

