### Patient measures

Table 3 provides details on planned patient measures and timing of administration. Participants complete a survey at baseline, two months, and six months after enrollment. Participants complete the surveys over the telephone with research assistants. We make 10 attempts over one month to reach participants to complete the surveys. The surveys include a demographics questionnaire designed by the study team; a smoking behavior and history questionnaire designed by the study team; the BASIS-24 scale measuring recent mental health functioning [22]; an impulsivity scale [23]; a functional health literacy scale [24]; measures of readiness to quit, motivation, self-efficacy, and attitudes about smoking developed by the study team; and satisfaction with treatment received from the TeleQuitMH program.

**Table 3 T3:** Patient measures and assessment schedule

**Measures**	**BL**	**2m**	**6m**
Sociodemographics	X		
Current and historical smoking behavior	X	X	X
Readiness to quit	X	X	X
Quitting self-efficacy and motivation	X	X	X
Medication assessment: Current use, contraindications to NRT or Bupropion	X		
Use of prior smoking cessation treatment	X	X	X
Nicotine dependence	X	X	X
Alcohol and substance abuse	X	X	X
Smoking environment: Social support for quitting, household smokers, household smoking rules, employer smoker rules	X		
Attitudes about smoking	X		
Mental health symptoms (BASIS-24)	X	X	X
Health literacy	X		
Impulsivity	X		
Patient satisfaction with the program		X	X
Patient assessment of treatment fidelity/counseling content		X	X

*BL* = baseline; *2m* = two months after enrollment; *6m* = six months after enrollment.

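### Aim 3 power and logistic regression treat VA-arm outcomes as independent, although each VA-arm patient is assigned to a shared counselor

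*Protocol article*

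**What the plan says.** The Effectiveness section of the protocol article sets the Aim 3 comparison and its power. The planning rates are given as "We expect the six-month abstinence rate will be 15% in the quitline arm and 20% in the VA arm", and the claim is "With an anticipated 1200 participants in each treatment arm, we will have >80% power to detect this 5% difference in abstinence rates", with the test "between the two arms at the 0.05 significance level". For the analysis, the abstinence rates are calculated by arm and the authors will "compare these rates using logistic regression, adjusting for covariables". The covariables are not named for Aim 3.

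The Participants section shows that 1,200 per arm is the number expected to enroll and be randomized. Allocation is by patient (Overview: "In a one-to-one fashion, we randomize patients").

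In the section on the clinical intervention, VA-arm patients receive individual counseling: "they are assigned a VA counselor trained to work with smokers who have a mental health diagnosis". The schedule is one to six planning sessions plus seven calls from the quit date onward. Quitline-arm patients are transferred once, and study staff then take no part in their counseling.

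On follow-up, the Patient measures section says: "We make 10 attempts over one month to reach participants to complete the surveys". The limitations in the Discussion mention variation between quitlines and unknown quitline intensity, but not counselor effects.

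**The concern.** Patients are randomized individually, but in one arm the treatment is delivered by counselors who each see many patients. This is a partially nested design: outcomes may be correlated within counselor in the VA arm and have no corresponding study-counselor grouping in the quitline arm. Motivational interviewing and problem-solving work are treatments in which the counselor's skill could plausibly affect the result.

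A logistic regression that treats all patients as independent leaves counselor variance out of the standard error. Patient-level covariates do not put it back. If that variance is not negligible, the confidence interval for the arm effect is too narrow, the test rejects too often under the null, and real power is below the independent-patient value. This is the trial's only randomized comparison. When each counselor has a large caseload, a very small ICC is enough to matter.

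**Working it through.** **Inputs from the article:** 15% versus 20%, 1,200 per arm, 1:1 allocation, alpha 0.05 (taken as two-sided because sidedness is not stated).

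**Inputs not in the article (assumptions):** number of VA counselors K from 4 to 20, ICC from near 0 to 0.01, and six-month loss from 0 to 30%.

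**1. The plan's own figure.** Mean rate 0.175.
- Null standard error: sqrt(0.175 × 0.825 × 2/1200) = 0.01551.
- Alternative standard error: sqrt((0.15 × 0.85 + 0.20 × 0.80)/1200) = 0.01548.
- Power: Φ((0.05 − 1.96 × 0.01551)/0.01548) = 89.7% (88.7% with continuity correction).

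The claim of more than 80% is reproduced. The same formula needs 906 per arm for 80%.

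**2. Loss alone.** 1 − 906/1200 = 24.5%, so on complete cases power stays at or above 80% up to that loss (82.3% at 20% loss, 77.0% at 30%). If non-responders count as smokers, both rates shrink by the response fraction; power is 80.6% at 20% loss and crosses 80% at about 21%.

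**3. Counselor clustering in the VA arm only.** Caseload m = 1200/K. Design effect DE = 1 + (m − 1) × ICC multiplies the VA-arm variance term. The standard error of the difference grows by about sqrt((1 + DE)/2). The true two-sided error of a test that ignores this is 2 × (1 − Φ(1.96 × sqrt(2/(1 + DE)))).

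Example with K = 6 and ICC 0.005: m = 200 and DE = 1 + 199 × 0.005 = 1.995. The standard errors become 0.01898 (null) and 0.01929 (alternative). Power is Φ((0.05 − 1.96 × 0.01898)/0.01929) = 74.6%, or 73.6% with the unpooled standard error throughout. The unadjusted test's error is 2 × (1 − Φ(1.96 × sqrt(2/2.995))) = 10.9%.

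| Counselors (assumed) | ICC (assumed) | DE | Power, no loss (unpooled to pooled) | Type I error, unadjusted test |
|---|---|---|---|---|
| any | 0 | 1.00 | 90% | 5.0% |
| 6 | 0.005 | 2.00 | 74–75% | 10.9% |
| 6 | 0.01 | 2.99 | 60–62% | 16.5% |
| 12 | 0.005 | 1.50 | 82% | 7.9% |
| 20 | 0.005 | 1.30 | 85% | 6.7% |
| 20 | 0.01 | 1.59 | 80–81% | 8.5% |

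**4. Where power reaches 80%.** With no loss, the ICC at which power falls to 80% is about 0.0021 (4 counselors), 0.0032 (6), 0.0053 (10) and 0.0107 (20). With 20% loss it is about 0.0005, 0.0007, 0.0012 and 0.0025.

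These are normal approximations with equal caseloads. With few counselors, limited degrees of freedom would lower power further.

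**The case against.** The strongest reply is that the article states no wrong number. More than 80% is a lower bound with about 10 points of slack, and it survives several of the scenarios above. That stands. A reader might infer that the power claim is wrong because it counts enrolled patients and some will miss the six-month call. The article does not support that: it gives no retention rate, the claim holds up to about 24.5% loss (about 21% if missing counts as smoking), and the slack may have been meant as an allowance.

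Second, neither the counselor number nor the ICC is documented. A reader might infer few counselors from the weekly group supervision, but that is only compatible with a small number and does not establish one. The training, standardized-patient checks, documentation audits and supervision are also meant to limit differences between counselors. This stands too, so the size must be given as a range.

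Third, if inference is confined to the counselors actually employed, patient-level variance is defensible. This is partly a choice of target. But the trial is presented as informing routine care, and that question reaches beyond these individuals.

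Fourth, the covariables are unnamed, and a fuller plan may deal with counselors. That limits the point to what the article fixes. It does not change the basis of the published power figure, which has no clustering term.

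**Conclusion.** The point holds in conditional form. The power statement is arithmetically correct, and attrition alone is not an error. What remains is that the article describes counselor-nested treatment in one arm, while its stated model and power figure rest on independent outcomes. If counselors differ in results, the Aim 3 standard error is understated and power is below the implied value.

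The size rests wholly on assumed counselor number and ICC. It runs from nothing at an ICC near zero, through modest (12 counselors at ICC 0.005, or 20 at 0.01: power still about 80 to 82%, unadjusted error about 8 to 8.5%), to material (6 counselors at ICC 0.005: about 74% and 11%). A reader might go further and conclude that type I error will exceed 5% or that power is below 80%. The article does not give the figures needed to say either. The change is still worth making, because it protects the only randomized comparison at little cost.

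**What to change.** 1. Analyse six-month Aim 3 abstinence with a model that allows for counselor clustering in the VA arm only. One option is a partially nested mixed logistic model with a random counselor effect in that arm and a small-sample correction such as Satterthwaite, so that the degrees of freedom come from the data and are not fixed at the counselor count.
2. Label the power figure (about 90%) as the value with no counselor clustering and no loss. Add a short table over counselor number, ICC and six-month response, and state the planned counselor number and expected response.

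Cost: a change to the analysis wording and one table. Counselor identity should be recoverable from the call-documentation template and the progress notes. No extra patients are asked for, but the rewording does not restore power that clustering would remove. Intervals would be somewhat wider, the counselor variance would be imprecisely estimated if counselors are few, and the power figure would look less favorable.

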#### Adoption

We will calculate program adoption by providers and patients across all sites and for each site separately. For this study, *adoption by a provider* will be defined as referring one or more patients to the TeleQuitMH program; i.e., the provider used our provider-level intervention of adapting the EMR to enable referrals. To calculate the program adoption by providers, we will generate a list of all mental health providers at each site using administrative records and a list of all mental health providers who made at least one referral using study data. We will then divide the number of providers who made at least one referral by the total number of providers. *Adoption by a patient* will be defined as enrolling in treatment. We will have a list of all patients referred to TeleQuitMH and the list of patients who enroll in treatment. We will divide the number of patients who enroll in treatment by the total number of patients referred to the program.

#### Implementation and maintenance

We will assess the program *implementation* at each site by examining the activities occurring at each site. There are eight main implementation activities that need to be completed to fully implement the TeleQuitMH program at a site (Table 5). We will score each site on the completion, fidelity, and intensity of each of these eight activities using anchors developed by the study team. We will assess program *maintenance* by examining monthly referral rates to examine time trends in referrals and whether patients and providers continue to use the program for the full intervention period.

**Table 5 T5:** Major TeleQuitMH implementation activities at each site

1. Designation of a local champion for the program	
2. Creation of a site Clinical Advisory Committee	
3. Creation of site prescribing structure	
4. Modification of EMR system to enable referrals and local documentation of treatment delivery	
5. Permission and process to make warm-transfers of patients to the state quitline	
6. Program marketing to providers	
7. Provider referrals	
8. Delivery of smoking cessation counseling and smoking cessation medications to enrolled patients.	

### Formative evaluation analyses

#### Developmental phase

Baseline provider survey and stakeholder interview data on attitudes toward smoking cessation and perceived barriers to telephone smoking cessation will be used to refine the implementation of the intervention. Documentation of the core structural components of the implementation at each site (e.g., prescribing structure, pre-existing smoking cessation services, characteristics of local champion) will be used to ensure the best possible implementation given site circumstances.

#### Implementation/progress focuses

Referral rates, treatment uptake and exposure at the patient level, and responses to TeleQuitMH at the provider level (collected via surveys, stakeholder interviews, and referral rates/patterns), will be continuously monitored to track program progress and identify sites that may need additional activities and efforts focused on facilitating implementation. Information on the structure of the implementation as it unfolds will be reviewed at regular staff meetings and linked with initial patient (enrollment rates, satisfaction) and provider process data (referral rates and patterns) to determine next steps for implementation including directed outreach/marketing; changes in structure, etc.

#### Interpretation/sustainability phase

After the intervention period has ended at each site, we will use the *interpretation/sustainability phase* of our formative evaluation to interpret primary outcomes, using qualitative pattern-matching approaches to explore how the implementation activities and structure of the implementation (including treatment fidelity) may help explain variations in outcomes at the site level. Similarly, data on the implementation context will be analyzed to determine variation across sites and whether that variation is associated with both the nature of the implementation and the outcomes achieved. Formative evaluation data will be analyzed longitudinally to determine if changes in implementation are associated with changes in process variables (e.g., reach, uptake). In terms of sustainability, analyses will focus on identifying the site and implementation features and characteristics that facilitated and hampered effectiveness. Finally, descriptions of the degree to which core elements of TeleQuitMH were integrated into systems of care at each site will be used to characterize the sustainability of TeleQuitMH and to identify the local conditions which facilitate replication and dissemination.

### Economic evaluation

It is not within the scope of this project to conduct a cost-effectiveness analysis. For this project, we will assess the costs involved with the TeleQuitMH program, including staff costs (salary and fringe benefits), cost of smoking cessation medications, and VA overhead. We will use data from the VA’s Decision Support System for the costs of provider time and smoking cessation medications. We will calculate the cost associated with counseling delivery using study administrative records for the VA counseling arm and quitline program estimates for the quitline arm. We will use VA rental space agreements at our primary site to estimate the cost of VA overhead associated with the program.

## Discussion

It can take 17 years for new clinical interventions to make their way through the efficacy-effectiveness-implementation research pipeline and become usual clinical care that improves patient outcomes in routine practice settings [29]. Hybrid effectiveness-implementation study designs offer the potential to greatly shorten this translation time [19]. This study utilizes an innovative hybrid design to concurrently study the clinical outcomes and implementation into routine care of a smoking cessation telephone care coordination program for mental health patients in six VA facilities. The study will study the clinical effectiveness of the care coordination program and compare the effectivness of two models for connecting mental health patients to telephone smoking cessation counseling (a tailored VA-staffed program versus a warm-transfer of patients to their state quitline), while producing important data about the acceptability and feasibility of telephone-based smoking cessation treatment among mental health providers and patients. Formative evaluation data collected during study start-up and regularly throughout the intervention period will help future tobacco control efforts in mental health treatment settings by identifying barriers to and facilitators of successful treatment program implementation.

The study will have several limitations. First, we will rely on self-reported abstience, which may produce over-estimates of short- and long-term quit rates among participants. Second, there is considerable variability in services provided by the quitlines, and we will not have sufficient power to conduct Aim 3 analyses separately for each state. Third, we randomize at the patient-level and will not be able to determine the effectiveness of our implementation strategies. However, researchers can use the qualitative and nonrandomized implementation outcomes data collected during the trial to design future group-randomized studies evaluating the effectiveness of different stratagies for implementing tobacco cessation treatment programs in mental health clinics. Lastly, we will not have data on the number or duration of counseling sessions provided to participants connected to the quitlines for counseling, so we will be unable to account for treatment intensity in our Aim 3 analyses.
